
### Study procedures

On-the-job training to strengthen the delivery of fully integrated ANC/MNCH/HIV clinical services will be conducted. Refresher trainings for health care providers at study sites will cover the components of high-quality ANC, PMTCT, and HIV treatment for pregnant women; early infant diagnosis; care and treatment for HIV-exposed infants and HIV-infected children; and postpartum family planning.

Study interventions will begin during pregnancy when the participant is enrolled and continue up to12 months postpartum. Blood sampling and laboratory testing required for primary and secondary study outcomes, including HIV testing for pregnant women and exposed infants, maternal CD4 counts, and viral loads, will be conducted as part of routine care per Kenya National ART guidelines by health facility staff.

We will also establish a Community Advisory Group (CAG) composed of local health workers, community leaders, representatives of community groups, and persons living with HIV in the study communities. This group will be invited to participate in a multi-day workshop to discuss the study plans, refine the content of community outreach messages, and discuss the cMM intervention; as well as in regular meetings throughout the study period. We will work with the CAG to develop methods for introducing the study, obtaining local support, and keeping communities informed about study progress and results.

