### Primary analyses

Preliminary analyses will summarize characteristics of the intervention and control women and assess frequency distributions of variables to identify outlying or unusual values. Initial analyses of our primary outcomes of maternal ART adherence and maternal retention in care (dichotomous variables) will be based on comparisons of proportions between intervention and control groups using cluster-adjusted chi square tests. Although there are only 24 clusters, each mean or percentage will be based on a relatively large number of women, and the normal approximation to the binomial distribution can be used. These tests will be evaluated based on a two-sided alternative hypothesis with a 5% type I error rate. Given the clustered study design, generalized estimating equation (GEE) models will be used to test for differences of interest in univariate and multi-variable models, adjusted for relevant covariates (such as time on ART), using logistic links for these binary outcomes. Secondary outcomes, such as time to infant testing uptake, maternal viral load suppression, and changes in maternal CD4 counts, will be analyzed using similar methods, taking into account the nature of the dependent variable (continuous, dichotomous, or time to event). Results will be summarized as odds ratios for models based on binary responses (e.g., enrollment in HIV care), hazard ratios for time-to-event outcomes (e.g., time to infant HIV test), and mean changes for continuous responses (e.g., maternal CD4 count); respective 95% confidence intervals will also be reported based on the robust variance estimates from the GEE models.

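### Maternal CD4 is specified as a mean change without a commitment to baseline CD4 as a covariate; naming it would make the comparison more precise at no cost

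*Protocol article*

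**What the plan says.** All of this stands in the protocol article, Methods/design.

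- Under Primary analyses, the secondary outcomes include "changes in maternal CD4 counts, will be analyzed using similar methods" to those for the primary outcomes, allowing for the type of variable.
- The same paragraph gives the effect summary for continuous outcomes: "mean changes for continuous responses (e.g., maternal CD4 count"). Intervals are "based on the robust variance estimates from the GEE models".
- The methods carried over are GEE in "univariate and multi-variable models, adjusted for relevant covariates (such as time on ART"). Time on ART is given as an example, so the list is open. Baseline CD4 does not appear in it and is not ruled out.
- Under Study procedures, "maternal CD4 counts, and viral loads, will be conducted as part of routine care per Kenya National ART guidelines". The text gives no CD4 time points, standard deviation, correlation or power; the schedule figure is not reproduced in the text at hand.

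**The concern.** A change in CD4 can be computed only for a woman who has a baseline value, so the most informative covariate for her later CD4 is already in the data set. The article commits to subtracting that value and does not commit to adjusting for it. Subtraction assumes in effect that a difference of one cell at baseline carries over as one full cell at follow-up. When the correlation is below 1, with similar variances at both times, it carries over as less than one, and subtraction overcorrects.

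At stake is the width of the CD4 interval, and how far a baseline difference between arms moves the estimate. Such a difference is plausible: the article itself remarks "Although there are only 24 clusters", and the women include both those newly starting ART and those already on it. Leaving the covariate open also leaves an unadjusted and an adjusted result, which may differ by several cells, with neither designated as the main one.

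**Working it through.** **The plan's own figures.** None concerns CD4. The sample size rests on the two primary outcomes. For retention, 48% v 73% at 80% power and two-sided 5% with continuity correction needs 67 per group. With mean cluster size 70, ICC 0.12 and a coefficient of variation of cluster size of ((130 - 50)/4)/70 = 0.286 (my reading of the stated range), the design effect is 1 + ((1 + 0.286²) × 70 - 1) × 0.12 = 9.966. Then 67 × 9.966 rounds to 668, and 2 × 668 = 1336, as in Table 1. No CD4 quantity enters, so nothing below touches that target.

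**Precision.** Let CD4 have the same variance σ² at both times and correlation r.

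- Unadjusted change: variance proportional to 2σ²(1 - r).
- Adjusted for baseline: variance proportional to σ²(1 - r²).
- Ratio, change to adjusted: 2/(1 + r). The standard error ratio is its square root.

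| Assumed r | Variance ratio | Standard error larger by |
|---|---|---|
| 0.3 | 1.54 | 24% |
| 0.5 | 1.33 | 15% |
| 0.7 | 1.18 | 8% |
| 0.8 | 1.11 | 5% |
| 0.9 | 1.05 | 3% |

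The formula ignores between-site variance. A simulation of 24 sites of 56 women (12 v 12, assumed ICC 0.05, assumed SD 200 cells, no true effect) gave standard errors of 16.1 and 14.9 at r = 0.7 (ratio 1.08) and 13.5 and 12.9 at r = 0.8 (ratio 1.04). These are close to the table.

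**Baseline imbalance.** Given a baseline difference d between arms, the unadjusted change estimate shifts by -(1 - r)d. Simulated slopes on d were -0.71, -0.52, -0.29 and -0.18 at r = 0.3, 0.5, 0.7 and 0.8; the adjusted estimate had slopes of about zero. For a main effect, with 1336/24 = 55.7 women per site and SD 200 (assumed), the standard deviation of d is 200 × √[(1 + 54.7 × ICC) × 4/1336].

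| Assumed ICC | SD of d (cells) | Typical shift, r = 0.5 | r = 0.7 | r = 0.8 |
|---|---|---|---|---|
| 0.01 | 13.6 | 6.8 | 4.1 | 2.7 |
| 0.05 | 21.1 | 10.6 | 6.3 | 4.2 |
| 0.12 | 30.1 | 15.0 | 9.0 | 6.0 |

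**These are one effect, not two.** The excess variance is 2(1 - r) - (1 - r²) = (1 - r)², which is the squared shift per unit of d. In the simulation at r = 0.7, √(16.13² - 14.91²) is about 6.2 cells, against 6.3 in the table. The loss of precision is the imbalance shift averaged over randomisations, so the two must not be added.

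**Change or follow-up as the outcome.** If change = a + b × arm + c × baseline, then follow-up = a + b × arm + (c + 1) × baseline. The intervention coefficient b is the same. In simulation the two differed by at most about 3 × 10⁻¹³, which is rounding error.

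**The case against.** The strongest reply is that the article does not fix an unadjusted analysis. It plans multivariable models with an open covariate list, and the full list for a secondary outcome commonly belongs in an analysis plan, which is not shown. That is right as far as it goes. A reader might infer that CD4 will be compared by change scores in place of a baseline-adjusted analysis, or that choosing change is itself the error. The text supports neither: baseline CD4 is not excluded, and a change model that contains it loses nothing. What stands is narrower. The article does state the outcome form and the summary, and it does plan a univariate model, which for change in CD4 has no baseline term.

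A reader might also infer that regression to the mean biases the comparison. It does not. Over randomisations the unadjusted change comparison is unbiased, and simulated mean effects were within 1 cell of zero for both methods. The shift arises only given an imbalance. It is also modest: about 4 to 9 cells at r = 0.7, where standard errors over the simulated correlations ran from 13 to 25.

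A further inference would be that recruiting women at sites whose allocation is openly known makes baseline CD4 differ systematically. The documents do not show this, and if it happened, adjustment for baseline CD4 would not be certain to remove it. Finally, time on ART accounts for part of the difference between new and established ART users, but it does not replace a woman's own baseline CD4.

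**Conclusion.** The point holds as a minor, free improvement to one secondary outcome. The article specifies change in CD4 and mean change as its summary without committing to baseline CD4 as a covariate. Where the comparison is unadjusted, its standard error is about 5% to 15% larger than it need be for r between 0.8 and 0.5, and the estimate carries any chance baseline difference in the proportion -(1 - r).

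These sizes rest on an assumed correlation, equal variances at the two times and, for the shifts in cells, an assumed SD of 200 and ICC of 0.01 to 0.12; none of these CD4 values is in the documents. If the multivariable model already includes baseline CD4, the adjusted result suffers no loss, and all that is missing is the statement that it is the main one.

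**What to change.** State that the main CD4 comparison is an identity-link GEE with the randomised factors and baseline CD4 as a covariate. Time on ART and other planned covariates can remain. Report the adjusted mean difference with its 95% interval. Either follow-up CD4 or change may be the outcome, since the effect is the same. Unadjusted mean change by arm can be kept as a descriptive figure.

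The cost is one term in a model already planned. It needs no new measurement and drops no further women, because anyone with a computable change has a baseline value. The primary analyses and the sample size need no revision.

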### Secondary analyses

Past research with this population suggests that, in spite of our best efforts, we will be unable to locate some individuals for follow-up, perhaps as many as 20%. We will gauge the impact on our study in two ways. First, we will perform multiple imputations under the missing-at-random (MAR) assumption. Our imputation model will include the rich array of baseline covariates collected; in that context, MAR would mean that women we locate are representative of women with the same observed characteristics whom we cannot locate. This assumption is superior to a range of other ad hoc methods; however, the MAR assumption is untestable [34, 35]. For that reason, we will also examine the sensitivity of our findings to violations of the MAR assumption, the so-called non-ignorable non-response. We will also consider inverse probability of censoring weighting (IPCW), which is regression analysis inversely weighted by the probability of participation; it is determined using a logistic regression model for probability of participation given baseline or previous history of covariates and outcomes. IPCW inflates the impact of underrepresented subjects, so we can observe associations that would have been observed if all subjects had stayed in the study to completion.

## Discussion

This study will determine the impact of long-term (up to 12 months postpartum) text messaging and cMMs on retention in and adherence to ART among pregnant and breastfeeding women living with HIV in Kenya. It will address key gaps in our understanding of what interventions may successfully promote long-term retention in the PMTCT cascade of care. While support among women living with HIV appears to be high for Option B+, high rates of “non-starters” (women who default after first visit) and losses of up to a third of women on ART are concerning [36–39]. The full benefits of Option B+ can only be realized if women are adherent to ART during pregnancy, breastfeeding, and throughout life.

Community-based strategies have the potential to enhance adherence and retention. Most countries in sub-Saharan Africa utilize community or lay health workers to support HIV services. However these workers may or may not be people living with HIV (PLHIV), and the majority are facility-based. While this has its benefits, the WHO and UNAIDS strongly recommend involvement of PLHIV in their own care [40]. Models utilizing PLHIV to support HIV services, such as peer navigators or the Mother-to-Mother program specifically for PMTCT, have shown some benefit but require rigorous evaluation. Our study will be able to determine the separate and combined effectiveness of cMMs and text messages specifically for women on Option B+.

In Kenya, a country of 43 million people, there are currently 37.8 million active mobile phone subscriptions, representing about 88% of the population [41]. While access to a mobile phone is significantly associated with postpartum retention in PMTCT [42–44], there are few studies evaluating the long-term impact of mobile phone technologies on improving long-term retention and adherence in the context of Option B+. One cluster randomized trial of text messages to support PMTCT care in Kenya did not demonstrate increased uptake of PMTCT services such as ART uptake, facility delivery, or infant testing, but it did not study the effects long term [45]. Another recent randomized trial in Kenya used behavior-based text messaging to improve uptake of early infant diagnosis and postnatal retention [23]. Our study will build on the results of this successful trial by using theory-based behavior text messaging to support long-term adherence and retention in the context of Option B+.

The use of the 2 × 2 factorial design will allow us to examine the individual effects of each intervention, as well as the potential combined effects when both interventions are introduced in the same community. Although the interventions we will test alone and in combination have been used in sub-Saharan Africa and are evidence-based, we will include some novel aspects that our prior research suggests will make these interventions even more effective. These include basing mentor mothers in the community rather than at the health facility and focusing their activities on HIV prevention and treatment behaviors as well as support for adherence and retention among women and children. Similarly, our mobile phone intervention will extend beyond the short-term interventions that have previously been tested for PMTCT to continue for a minimum of 12 months and will include unique theory-based content as well as bi-directional communication to support long-term adherence and retention.

Our study has a number of limitations. First, it is being conducted in an environment where study sites are implementing other interventions simultaneously. This might attenuate the effect of our intervention. Second, policy and service changes are constantly occurring within the PMTCT field which might interact with our intervention in unknown ways. However, we feel that operating in an environment with other simultaneous interventions and changing policies reflects “real-world” implementation of our interventions and therefore enhances external validity. Finally, our study relies on medical records and a single-item self-report of ART adherence. This method carries biases that might result in inaccurate measurement of medication adherence. To address this limitation, we will also measure HIV viral load, which is a biological measure that is less prone to bias.

In summary, this trial uses novel interventions and research methods to study an issue in a setting where lifelong ART for women living with HIV (Option B+) has recently been rolled out countrywide and has not been studied. Our study will provide important guidance for similar countries in sub-Saharan Africa by identifying effective and scalable interventions and combinations of interventions that can reduce barriers and increase facilitators of optimal ART adherence and retention in care for pregnant and breastfeeding women on ART. The aims are to reach the elimination of mother-to-child transmission of HIV and significantly improve maternal health.

## Trial status

The MOTIVATE! study is currently in month 44 of 60 planned months of recruitment and data collection. A populated Standard Protocol Items: Recommendations for Interventional Trials (SPIRIT) checklist and a figure describing the study protocol are included as Additional file 1 and Fig. 2. The flow diagram is presented in Fig. 3.

**Fig. 2 Fig2:**
[figure not shown]
Standard Protocol Items: Recommendations for Interventional Trials Statement (SPIRIT) figure for the MOTIVATE! study. Schedule of enrollment, intervention and assessments

**Fig. 3 Fig3:**
[figure not shown]
Flow Diagram for the MOTIVATE! study

## Abbreviations

ART: Antiretroviral therapy
cMM: Community-based mentor mother
MOTIVATE!: Mother and Infant Visit Adherence and Treatment Engagement (study)
Option B+: Lifelong ART for women living with HIV
PMTCT: Maternal and child health prevention of mother-to-child HIV transmission
SMS: Short message service
